**Fig. 1 fig0005:**

Intervention schedule.

The baseline measurements will be distributed at week 1 as follows. At the 1st HD session of the week the resting HR, resting blood pressure, ankle-arm index (AAI) measurements and questionnaire application will be performed. At the 2nd HD session of the week the percentage of fat, body mass and height measures, and blood collection will be obtained, after the HD session. At the 3rd HD session of the week the functional capacity (using the 6-minute walk test) and muscle strength (using dynamometry) will be measured. The final evaluations (post-intervention) will follow the same weekly distribution of the baseline measures.

Blood pressure will be measured with an accurate analog sphygmomanometer (accuracy of 1.0 mm/Hg) and stethoscope (BD, Brazil). Body mass and height will be measured using digital electronic anthropometric scale with a resolution of 0.1 kg and 0.1 cm, respectively (Filizola, Brazil). Body mass index (BMI) will be calculated based on body mass and height. The HR will be measured using a digital HR monitor (Polar, Finland).

To calculate ankle-arm index (AAI) the patient should rest supine for at least 10 min before testing, the systolic blood pressure measurement will be performed in the upper limb using an analog sphygmomanometer. The measure will be performed on the arm that is not with the dialysis fistula. The systolic blood pressure at the ankles will be measured using the vascular Doppler with transducer of 5–8 MHz with application of gel on the analyzed region and the same model of sphygmomanometer as previously reported [9]. The cuff will be placed about three inches above the malleolus. The following formula will be applied to calculate AAI: AAI = higher ankle pressure x higher arm pressure^−1^ [9].

The femoral quadriceps muscle thickness will be measured by MicroMaxx(Sonosite®) ultrasound, according to a protocol proposed by Paris et al. [10] Two reference points on the anterior surface of each quadriceps will be identified and marked with an indelible ink pen: the first one on the midpoint between the anterior superior iliac spine and the upper pole of the patella and the second on the border of the lower third and upper two thirds between the upper anterior iliac spine and the upper pole of the patella [9]. The muscle thickness will be quantified using the frozen image on the screen considering the distance between the upper margin of the femoral bone and the lower limit of the deep fascia of the *rectus femoris*, incorporating both *rectus femoris* and the *vastus medialis* skeletal muscles.

The percentage of fat will be estimated by body composition analysis using multifrequency bioelectrical impedance analysis (Quadscan4000, Bodystat®), according to recommendations and a protocol previously published by Kyle et al.: in supine body position, arms stretched along the trunk and legs apart. The electrodes will be placed respecting the distance of at least 5 cm on the previously cleaned skin using alcohol. The assessment will be performed 20 to 30 min after the middle-week HD session, being important to protocol the day and time of the measurements, as well as a period of a few minutes post-dialysis to balance the fluid concentrations of the body compartments [11]. The percentage of body fat will be estimated using the manufacturer’s equation.

Considering the measurement of body composition and quadriceps femoral muscle thickness, patients will be instructed to avoid physical exercise practice eight hours before and avoid consuming alcohol, chocolate, coffee, tea and energy drinks in the 12 hs prior to the exam. Body composition and muscle thickness will be measured between 20–30 min after the HD session, as recommended by Kyle et al. [11].

A trained nurse will draw 10 mL of blood directly from intravenous fistula, 5 mL in the tube with clot activator and another 5 mL in the anticoagulant tube. The blood will be separated and stored. The erythrocytes fraction will be isolated and stored to oxidative stress analyses. Blood samples will be collected at baseline and repeated after the third training session (baseline blood lactate concentration after training) and after the end of the last training session of each training mesocycle, at the end of weeks six and twelve, respectively. The last blood collection will be performed 48 h after the last exercise session, to avoid acute effects of the exercise influencing inflammatory and oxidative stress markers (Fig. 2).

**Fig. 2 fig0010:**
[figure not shown]
Schedule of blood collections.

Serum levels of IL-6, IL-10, and CRP will be measured using immunoassay kit (DuoSet ELISA Development, R&D Systems, Inc., USA). These methods will follow the manufacturer's recommendations. The amount of IL-6, IL-10, and CRP will be determined by measuring the absorbance at 450 nm. All samples and standards will be measured in duplicate, and the coefficient of variation will be less than 5%. The IL-6, IL-10, and CRP levels will be expressed in pg/mL.

Oxidative stress markers (catalase, peroxide dismutase, and glutathione peroxidase enzymes) will be measured using a commercially available kit (RANSEL®; Randox Lab, Antrim, United Kingdom), using the method described by Misra and Fridovich [12].

The 6-minute walk test will be conducted on a 30-meter flat track, demarcated every three meters. Before starting the test, patients will remain seated for 10 min to stabilize vital signs. The patient will be advised to walk for 6 min, from one end of the lane to the other, at the highest possible speed. This test will be performed before the HD session, since patients cannot walk well after the HD session due to the loss of fluid with hypotensive effects [13].

The static strength testing of lower limbs will be performed with a Crown® brand dynamometer. Initially, patients will be instructed to stand on the base of the device, flexed knees forming an angle of approximately 120°, upright spine, arms along the body and extended elbows. After resetting the instrument, the subjects should perform the maximum knee extension force possible, avoiding any movement with the spine or arms and moving the body backwards. Two measurements will be performed with a 1 min interval between them. The mean of these two measures will be used as a result [14].

After baseline collection, participants will be allocated randomly: 1) BFRG; 2) EG; 3) CG. The intervention will last twelve weeks divided into three weekly sessions, always having at least a day interval between sessions. All physical exercise sessions will be monitored by physical therapists and physical education teachers to guarantee the perfect execution of the exercises and the correct use of the BFR accessory and heart monitor.

### Intervention description

The physical exercise groups – BFRG and EG – will be submitted to an exercise protocol composed by 20 min on the stationary bicycle. The exercise will be performed in the first two hours of HD to avoid hypotension effects that occur usually in the second half of the 4-hour session [1,3,15]. A cycle ergometer will be placed in front of the patient's chair and will be positioned at a distance allowing a relative knee angle (inner angle formed between the thigh and the leg) between 150° and 155° and using the following progression:

Mesocycle 1 – Weeks 1 to 6: participants will cycle at an intensity eliciting HR between 60 and 63% of HRmax or 10 to 11 in the perceived subjective exertion (PSE) scale, which ranges from 6 to 20 [16].

Mesocycle 2 – Weeks 5 to 8: participants will cycle at an intensity eliciting HR between 64 and 76% of HRmax or 12 to 13 in the PSE scale, which ranges from 6 to 20. [16] (Fig. 3).

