## Abstract

Chronic kidney disease (CKD) is associated with physical weakness and increased oxidative stress and inflammation levels. Rehabilitation programs are associated with an improvement in the functional capacity, inflammatory and oxidative stress profile. Exercise associated with blood flow restriction (BFR) has been demonstrating positive effects in training programs, but there is lack information about exercise with BFR in CKD. Therefore, the aim of the present study is to describe a protocol using continuous moderate exercise with blood flow restriction (BFR) applied during hemodialysis (HD) to measures health indicators and immune system and oxidative stress parameters in CKD patients. Methods: A RTC will be conducted with 42 patients in HD. Baseline measures will be compared with final measures (anthropometric, cardiorespiratory, biochemical, muscle fitness, nutritional and behavioral questions). Participants will be randomly allocated to: 1) Continuous moderate exercise group with BFR; 2) Continuous moderate exercise group without BFR; 3) Control group without exercise. The intervention will be 12 weeks long during HD session. Patients will perform 20 min of continuous moderate exercise on a stationary bicycle three times a week. The present study is expected to generate significant information about the role of exercise with BFR in patients with CKD during HD.

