**Fig. 3 fig0015:**
[figure not shown]
Training protocol.

The exercise sessions will use the following routine: 1) place the heart monitor on the chest of the subjects; 2) place the BFR equipment on their thighs while standing; 3) inflate the pressurized band to induce BFR while sitting in HD chair; 4) place the stationary bicycle in front of the patient; and 5) instruct patients to cycle.

The maximum HR will be determined using the following formula: HRmax = 211-(0.64 x age) [17]. Patients using medications influencing HR, such as beta-blockers, will have their HR corrected based on the study of Godoy [18].

A cycle ergometer will be placed in front of the patient's chair and will be positioned at a distance allowing a relative knee angle (inner angle formed between the thigh and the leg) between 150° and 155° [19].

The BFRG will perform the exercise with BFR, while the CG will perform with no BRF. For the BFRG, a 6 cm wide inflatable band will be placed at the root of the lower limbs and inflated according to the thigh circumference of the patients, as suggested by Loenneke et al. [15]. The following thigh circumference/pressure will be applied to impose 50% of arterial restriction: from 45 to 50.9 cm: 100 mmHg; to 51 from 55.9 cm: 130 mmHg; from 56 to 59.9 cm: 150 mmHg; ≥60 cm: 180 mmHg. The patient will maintain BFR throughout the exercise. The exercise will be interrupted if the patient shows any discomfort or wants to stop.

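### The intervention text contradicts itself on which weeks each intensity covers and on whether the control group exercises

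*Protocol article*

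**What the plan says.** **Length.** The Procedures section states: "The intervention will last twelve weeks divided into three weekly sessions". The Abstract and the Specifications Table also give 12 weeks.

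**Progression.** The Intervention description assigns one progression to both exercise arms, the arm with BFR (BFRG) and the arm without it (EG). Mesocycle 1 reads "Weeks 1 to 6: participants will cycle at an intensity eliciting HR between 60 and 63% of HRmax or 10 to 11" on the 6-to-20 exertion scale. Mesocycle 2 reads "Weeks 5 to 8: participants will cycle at an intensity eliciting HR between 64 and 76% of HRmax", with 12 to 13 on the same exertion scale as the alternative. The paragraph then points to Fig. 3 (Training protocol), which is not reproduced in the text at hand.

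**Blood sampling.** The blood-collection paragraph under Procedures places samples "after the end of the last training session of each training mesocycle, at the end of weeks six and twelve, respectively". It adds that the last draw comes 48 hours after the last exercise session.

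**Arms.** The Abstract lists "3) Control group without exercise", and the Specifications Table agrees. Table 1 codes the exposure as 0 for no exercise, 1 for exercise without BFR and 2 for exercise with BFR. The paragraph below Fig. 3 on delivering the restriction says instead: "The BFRG will perform the exercise with BFR, while the CG will perform with no BRF".

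**The concern.** These sentences are delivery instructions, and the article's declared aim is to describe the protocol, so they are its core content. The point does not concern detail that a condensed article leaves to a fuller document. The schedule and the arm roles are stated, and stated inconsistently.

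Two things are at stake. First, the exercise dose: someone delivering or replicating the programme from this text has two targets for some weeks and none for the last four, which come just before the final assessment. The phrase that ties blood samples to the end of each mesocycle also stops agreeing with the calendar weeks given beside it. Those samples serve the inflammatory and oxidative stress outcomes.

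Second, the control: comparing exercise with no exercise needs an unexposed arm. In the paragraph that separates the arms in practice, the only statement about who cycles without restriction names the CG and does not mention the EG.

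**Working it through.** **Inputs**
- 12 weeks, 3 sessions a week (Procedures).
- Mesocycle 1: weeks 1 to 6, 60 to 63% of HRmax or exertion 10 to 11. Mesocycle 2: weeks 5 to 8, 64 to 76% of HRmax or exertion 12 to 13 (Intervention description).
- Mesocycle ends at weeks 6 and 12 (blood-collection paragraph, Procedures).
- HRmax = 211 − 0.64 × age (Intervention description, below Fig. 3).

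**Step 1: count the sessions.** Total = 12 × 3 = 36.

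| Weeks | Targets in the text | Sessions |
|---|---|---|
| 1–4 | one (mesocycle 1) | 4 × 3 = 12 |
| 5–6 | two | 2 × 3 = 6 |
| 7–8 | one (mesocycle 2) | 2 × 3 = 6 |
| 9–12 | none | 4 × 3 = 12 |

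Sessions with exactly one target: 12 + 6 = 18. Sessions with two or none: 6 + 12 = 18. Share without a unique prescription: 18/36 = 50%.

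**Step 2: can both targets be met in weeks 5 and 6?** The age of 60 is chosen for illustration only. HRmax = 211 − 0.64 × 60 = 172.6 bpm.
- Mesocycle 1: 0.60 × 172.6 = 103.6 to 0.63 × 172.6 = 108.7 bpm.
- Mesocycle 2: 0.64 × 172.6 = 110.5 to 0.76 × 172.6 = 131.2 bpm.

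The bands do not overlap. The same holds at any age, because 63% is below 64%. The exertion ranges, 10 to 11 and 12 to 13, do not overlap either. Each target is given as heart rate or exertion, so a session could in principle meet one target on one scale and the other target on the other scale. On any single scale, however, the two targets are incompatible.

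**Step 3: set the mesocycle ends side by side.** Both places end mesocycle 1 at week 6. For mesocycle 2, the Intervention description gives week 8 and the blood-collection paragraph gives week 12, a difference of 12 − 8 = 4 weeks. As a consistency check only, ends at weeks 6 and 12 would put each of the 12 weeks in exactly one mesocycle. That shows the blood-collection paragraph fits the stated length. It does not settle which split is intended.

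**Step 4: set the arm statements side by side.**

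| Place | Control group | Exercise without BFR |
|---|---|---|
| Abstract, Specifications Table | no exercise | a separate group |
| Intervention description, opening | not among the exercise groups | EG |
| Table 1 | code 0, no exercise | code 1 |
| Paragraph below Fig. 3 | performs without BFR | CG |

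Read literally, the last row makes the CG the same as the EG and leaves no arm without exercise. Every other row contradicts it.

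**The case against.** A reader might infer that the three arms cannot be delivered or compared at all. The documents do not support that, for these reasons.

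- BFRG and EG share one written progression. The week error applies to both alike, and nothing in the text gives them different intensities. It does not by itself bias the comparison of exercise with and without BFR. That protection does assume that staff resolve the ambiguity in the same way in both arms.
- The control arm is recoverable. One sentence has it exercising, while the Abstract, the Specifications Table, the opening of the Intervention description and Table 1 say or imply otherwise. The Discussion also describes two exercise protocols, with and without BFR.
- A reader might also infer that the blood samples have lost their timing. They have not: the calendar weeks are stated, and so is the 48-hour interval before the last draw. Only the mesocycle label fails to match.
- Fig. 3 is not shown and may give the week-by-week schedule. The gap in weeks 9 to 12 and the 50% are established for the text only.
- This is a condensed article. The full protocol may be clear, sessions are supervised by professionals, and weekly staff meetings are planned. That staff had to improvise is therefore not shown.

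All of this stands, and it limits the consequence. It does not remove the contradictions. If Fig. 3 repeats the text, the gap remains; if it differs, the figure and the text disagree.

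**Conclusion.** Wrong as written on two operative points. In the text, 18 of 36 sessions (50%) have no unique intensity: 6 with two incompatible targets and 12 with none. The stated end of mesocycle 2 differs by four weeks between two sections. One delivery sentence contradicts at least four other places on whether the control group exercises and, taken literally, leaves no unexposed control.

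The consequence is an exercise dose that is not uniquely fixed, a mesocycle label that does not match the week-12 blood draw, and an arm instruction that could be misread. The contrast of BFRG with EG, the sample size (36, raised to 42) and the analysis model are not shown to be affected.

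The count assumes three sessions in every one of the 12 weeks, as stated, and covers the text without Fig. 3.

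**What to change.** - **Weeks.** Reconcile the length of the intervention and the blood-collection paragraph (both under Procedures) with the mesocycle ranges in the Intervention description, and check Fig. 3 against the result. Each of weeks 1 to 12 should fall in exactly one mesocycle, and the mesocycle-end blood draws should match.
- **Arms.** Reconcile the sentence below Fig. 3 with the Abstract, the Specifications Table, the opening of the Intervention description and Table 1 on which arm exercises without BFR.

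Which intensity or week split is right is for the investigators to settle; none is proposed here. The cost is a correction of about one paragraph and a note to the staff who supervise sessions. It adds no patients, procedures or analyses.

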**Fig. 3 fig0015:**
[figure not shown]
Training protocol.

The exercise sessions will use the following routine: 1) place the heart monitor on the chest of the subjects; 2) place the BFR equipment on their thighs while standing; 3) inflate the pressurized band to induce BFR while sitting in HD chair; 4) place the stationary bicycle in front of the patient; and 5) instruct patients to cycle.

The maximum HR will be determined using the following formula: HRmax = 211-(0.64 x age) [17]. Patients using medications influencing HR, such as beta-blockers, will have their HR corrected based on the study of Godoy [18].

A cycle ergometer will be placed in front of the patient's chair and will be positioned at a distance allowing a relative knee angle (inner angle formed between the thigh and the leg) between 150° and 155° [19].

The BFRG will perform the exercise with BFR, while the CG will perform with no BRF. For the BFRG, a 6 cm wide inflatable band will be placed at the root of the lower limbs and inflated according to the thigh circumference of the patients, as suggested by Loenneke et al. [15]. The following thigh circumference/pressure will be applied to impose 50% of arterial restriction: from 45 to 50.9 cm: 100 mmHg; to 51 from 55.9 cm: 130 mmHg; from 56 to 59.9 cm: 150 mmHg; ≥60 cm: 180 mmHg. The patient will maintain BFR throughout the exercise. The exercise will be interrupted if the patient shows any discomfort or wants to stop.

### Study variables

The dependent variables of the study will be the health indicators (AAI, strength, functional capacity and quality of life), inflammatory variables (IL-6, IL-10 and CRP), oxidative stress (catalase, superoxide dismutase and glutathione peroxidase) and femoral quadriceps muscle thickness. The independent variable will be BFR, and the variables alcohol intake, diet, age, BMI and use of continuous medication, will be collected and considered in the analysis as possible confounders (Table 1).

**Table 1 tbl0005:** Dependent and independent study variables.

Variables	Definition	Scala	Operationalization
*Dependent*			
Interleukin 6	**Numeric**	**pg/ml**	---
Interleukin 10	**Numeric**	**pg/ml**	---
C-reactive protein	**Numeric**	**pg/ml**	---
Femoral quadriceps muscle thickness	**Numeric**	**mm**	---
Catalase activity	**Numeric**	**U/mg**	---
Superoxide dismutase activity	**Numeric**	**U/mg**	---
Glutathione peroxidase activity	**Numeric**	**U/mg**	---
Ankle-arm index	**Numeric**	**Ratio**	---
Functional test	**Numeric**	**Meters**	---
Strength	**Numeric**	**Lbs**	---
Quality of life	**Numeric**	**Score**	---
*Independent*			
Continuous moderate exercise intervention associated with partial blood flow restriction	Trichotomous	0, 1 or 2	**0 – Without exercise**
			**1- Exercise not using BFR**
			**2– Exercise using BFR**

BFR – Blood flow restriction.

#### Questionnaire

The questionnaire will consist of questions related to the following variables: age, sex, socioeconomic status, schooling, nutritional status, alcohol intake, continuous use medication, quality of life and 24-hour food recall. Continuous medicines use will be collected using an open-ended question asking whether the subjects use continuous medication and, if so, what the name of the drug is and the dosage taken. Quality of life will be evaluated using the Brazilian portuguese version of the Quality of Life Assessment of patients with CKD (KDQOL-SF™1.3) – instrument developed to evaluate the quality of life of individuals with CKD on dialysis [20]. It contains 79 items, 43 of which are related to CKD and 36 are related to general health condition.

### Data processing and analysis

The data will be doubled typed in EPIDATA 3.1 software, which will perform analysis to verify inconsistencies and correction of possible errors. The 5% significance level will be used and the statistical analysis will be conducted in Stata 14.0 software. The two mixed factors analysis of variance (ANOVA) will be used in the comparison of the training protocols, using Bonferroni as a post-hoc test for parametric variables. Kruskal-Wallis test and Dunn's post-hoc test will be used to non-parametric variables. The responsible researcher for the statistical analysis will be blinded regarding to the study objectives.

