### Sample size calculation

Sample size was calculated to estimate the occurrence of outcomes in each of the groups separately and to evaluate the association between each outcome: muscle thickness [5], IL-6 [6], TNF-alfa [7] and, quality of life [8], and the exposure variable. According to the largest sample size calculation, 36 patients would be required (to maintain a minimum power of 80% and a 95% confidence level). To compensate for possible losses and refusals, 42 patients will be included [[5], [6], [7], [8]].

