### Randomization

The randomization process will be performed using the generation of random numbers in the Stata software, version 13, and the researcher who will carry out the process will be blinded regarding to the study objectives. The randomization will be done in blocks, each block referring to the HD shift. In each block, the first patient drawn will go to the BFRG, the second to the EG, the third to the CG, and so on. In total, 14 patients will be drawn in each block to ensure balance between groups.

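### The group-by-time mixed ANOVA is valid, but it does not adjust for the baseline value or include the HD shift used in randomisation, so it gives up precision that could be had at almost no cost

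*Protocol article*

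**What the plan says.** The section Data processing and analysis of the Protocol article fixes the method: "The two mixed factors analysis of variance (ANOVA) will be used in the comparison of the training protocols", with Bonferroni post-hoc comparisons. For the remaining variables, "Kruskal-Wallis test and Dunn's post-hoc test will be used to non-parametric variables". On the error rate it says "The 5% significance level will be used". In this scheme the baseline measurement enters only as one level of the time factor.

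The Randomization section says "The randomization will be done in blocks, each block referring to the HD shift", and "In total, 14 patients will be drawn in each block to ensure balance between groups". With 42 patients that implies three shifts, since 42/14 = 3.

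The Study variables section names alcohol intake, diet, age, BMI and continuous medication, and says that they "will be collected and considered in the analysis as possible confounders". Neither the baseline value of the outcome nor HD shift is among them.

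The Sample size calculation section states "36 patients would be required (to maintain a minimum power of 80% and a 95% confidence level", and then "To compensate for possible losses and refusals, 42 patients will be included".

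**The concern.** The trial collects a baseline value for each outcome and arranges its randomisation by HD shift, but the stated analysis makes limited use of the first and none of the second. With two time points, the interaction in a two-factor mixed ANOVA subtracts the whole baseline value from the final value. Regression on baseline subtracts only the part that predicts the final value, so its residual variance is never larger, apart from the degree of freedom it spends.

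This matters because the trial is small. With 12 evaluable patients per arm, 80% power for a single pairwise contrast needs a standardised difference of about 1.2. Chance imbalance is also sizeable: the baseline difference between two arms of 14 has a standard deviation of sqrt(2/14) = 0.38 baseline SDs.

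A smaller matter is that the Study variables section promises to consider five covariates, while the analysis section names two procedures without covariates. No rule says which variables enter or how.

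**Working it through.** **Inputs from the article.** Required N 36 (12 per arm); enrolled N 42 (14 per arm on average); power 80%; significance level 5%, taken as two-sided because sidedness is not stated; randomisation blocks of 14 by HD shift.

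**Assumed inputs.** The article gives no effect size, SD, baseline-to-final correlation or shift effect. Rho is therefore varied from 0.3 to 0.9.

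**The plan's own figure.** The 36 cannot be reproduced without an effect size and SD. Solving backwards at 12 per arm, 80% power and two-sided 5%, it corresponds to a standardised difference of 1.20 for one pairwise t-test, or 1.41 with Bonferroni for three pairs. The step from 36 to 42 is an allowance of 1 - 36/42 = 14.3%.

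**Baseline adjustment.** Take outcome variance 1 at each time.

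- Change score: residual variance = 2(1 - rho).
- Adjusted for baseline: residual variance = 1 - rho² = (1 - rho)(1 + rho).
- Ratio = (1 + rho)/2.

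For power, start from a change-score contrast with 80% power at 12 per arm on 36 - 3 = 33 df, which needs a noncentrality of 2.886. Divide this by the square root of the ratio and evaluate on 32 df.

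| Assumed rho | Change variance | Adjusted variance | Ratio | Noncentrality | Power | 36 × ratio |
|---|---|---|---|---|---|---|
| 0.3 | 1.40 | 0.91 | 0.65 | 3.580 | 93% | 23.4 |
| 0.5 | 1.00 | 0.75 | 0.75 | 3.333 | 90% | 27.0 |
| 0.7 | 0.60 | 0.51 | 0.85 | 3.131 | 86% | 30.6 |
| 0.8 | 0.40 | 0.36 | 0.90 | 3.043 | 84% | 32.4 |
| 0.9 | 0.20 | 0.19 | 0.95 | 2.961 | 82% | 34.2 |

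Allowing also for the extra variance from chance baseline imbalance (a factor of 1 + 1/31) lowers the powers by about one point, to 92.7%, 88.9%, 84.8%, 82.7% and 80.7%. Spending two more df on shift changes them by less than 0.3 points.

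**HD shift.** A simulation used 42 patients in three shifts of 14. The stated sequence was applied within each shift (5:5:4), with rho 0.5, outcome variance 1 excluding shift, and 4,000 replicates per setting. The table gives the mean model standard error of one arm contrast.

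| Shift variance on level | Shift variance on change | Change score, no shift | Change score, with shift | Baseline-adjusted, no shift | Baseline-adjusted, with shift |
|---|---|---|---|---|---|
| 0 | 0 | 0.384 | 0.384 | 0.338 | 0.338 |
| 0.1 | 0 | 0.385 | 0.384 | 0.342 | 0.337 |
| 0.1 | 0.05 | 0.395 | 0.385 | 0.368 | 0.338 |
| 0.1 | 0.2 | 0.424 | 0.384 | 0.410 | 0.338 |

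A stable shift effect on level cancels from the change score, so leaving shift out costs the group-by-time test nothing (0.385 against 0.384). If shift predicts change, the model standard error is about 3% (0.395/0.385) to 10% (0.424/0.384) too large without it. Once baseline is a covariate, a level effect no longer cancels exactly, so shift belongs in the adjusted model. For a level effect alone that is worth only about 1% (0.342/0.337).

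**The case against.** The strongest reply is that the mixed ANOVA is a standard and valid pre/post analysis. The change-score contrast is unbiased under randomisation and has the correct type I error, and the article does not say that it is the most efficient choice. This stands, and it sets the weight of the point. The gain also rests wholly on rho. For a stable measure with rho near 0.9, power rises only from 80% to about 82%.

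A second reply is that a condensed article need not write out its covariates, and that the analysis section does not exclude them. This stands in part. The article does name both a model and a covariate list, and the two most useful terms are in neither. But the difference between the two sections is a loose end to reconcile, not a flat contradiction.

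Three stronger readings are tempting, and the documents do not support them:

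- A reader might infer that ignoring shift makes the standard errors too large and the test conservative. That is true for tests on outcome levels, such as the group main effect or a rank test on final values. For the group-by-time test it is true only if shift predicts change, and nothing in the article suggests that it does.
- A reader might infer that six of 42 patients are expected to be lost. The allowance covers possible losses and refusals together, so it is not a forecast of six missing final values.
- A reader might infer that regression on the final value solves missing data. It also drops patients without a final value.

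Finally, the two-time formula is only a simplification for the blood markers, which are sampled at more than two times.

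**Conclusion.** The point holds as an efficiency improvement. For outcomes measured at baseline and at the end, baseline adjustment cuts the variance of an arm contrast by 35% at rho 0.3, 25% at 0.5, 15% at 0.7, 10% at 0.8 and 5% at 0.9. Power rises from 80% to about 93%, 90%, 86%, 84% and 82% respectively. These figures assume equal variance at both times, 12 evaluable patients per arm, and a change-score test that starts at 80% power. The article gives neither rho nor an effect size, so they show a range, not a prediction for any one outcome.

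Including HD shift is right because the analysis should follow the randomisation. Its gain in precision is conditional and may be nil for the group-by-time test. Nothing here shows bias or an inflated error rate in the stated analysis, so the change is worth making but is not the correction of an error.

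**What to change.** For between-arm inference on the numeric outcomes, replace the group-by-time mixed ANOVA with a baseline-adjusted linear model containing arm, the baseline value of the same outcome and HD shift. If patients without a final value are to be included, fit it as a constrained-baseline mixed model, which also suits the blood markers with their additional time points. Report adjusted arm differences with 95% confidence intervals, and keep Bonferroni for the three pairwise contrasts.

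Say what role the Kruskal-Wallis and Dunn route keeps, since as written it carries neither a baseline nor a shift term.

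Reconcile the Study variables section with the analysis section: limit adjustment to baseline value, shift and any further baseline covariate named in advance, and drop the open-ended reference to possible confounders.

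The cost is analysis wording and about three degrees of freedom (one for baseline, two for three shifts). No new data are needed, because baseline values are already measured and shift is known from the randomisation.
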